## Discussion

The AFINOS Study is a multidisciplinary, multicentre study designed to tackle in adolescents multiple aspects related to the relationship between the level of daily physical activity and several health markers, specifically those related to the immune system, cardiovascular risk factors or being overweight or obese. The main characteristic of this study is its dual approach in that it examines a population sample of adolescents and a convenience sample of this population, which is subjected to a meticulous analysis of levels of physical activity, physical fitness and health status, including an extensive study of immunological variables. A further innovative feature is the collection of additional information about the adolescents' families, which will be used to find out how the family environment could affect the health status of the adolescents.

The main contributions and strengths of the study are as follows. From the population study, extensive information on health markers and healthy habits can be obtained via questionnaires, allowing for a good description of the current health conditions of adolescents from the Madrid region. Especially relevant is the evaluation of sedentarism and physical activity, which was assessed in the population sample through different groups of items within the general questionnaire and two specific detailed questionnaires. The capacity to evaluate these variables in the adolescent population of Spain will be established by comparing the data obtained in the questionnaires with the information supplied by the accelerometer and diary in the convenience sample. This will provide detailed patterns of physical activity for the adolescents of the Madrid region, and also give an idea of the relative risks associated with sedentarism of developing the health problems for which information was collected. Additionally, the information on academic performance will allow for assessment of possible relationships of regular physical activity with this factor. This issue is of interest for discussions related to implementing daily physical education programmes in schools [54]. The information gained on the adolescents' family environment will help assess possible effects on acquired health habits in the adolescents themselves, as well as the appearance of specific health problems. Additionally, if there is a sufficiently high response rate, it may be possible to estimate the prevalences of physical activity habits, sedentarism, and of specific health habits in the adult population of the Madrid region.

The major strength of the convenience study is its detailed assessment of the patterns of physical activity and sedentary behaviour in the sample examined based on the concurrent use of objective (accelerometry) and subjective (diaries and questionnaires) methods. This will allow for determining the validity of the different subjective assessment methods for use in the Spanish adolescent population. Until now, very few instruments had been validated to assess physical activity and sedentarism in Spanish children and adolescents. Consequently, one of the expected applications of the study's results is to increase the number of validated tools available for future use in epidemiological and clinical studies in Spanish adolescents. Another major strength of the study consists of the exhaustive assessment of immunological profiles, including an extensive set of immunologic variables, which to the best of our knowledge have not been determined in similar studies performed in Spain or Europe. Additionally, the study fairly exhaustively examines health related fitness, including body composition variables and at-rest blood pressures.

One of the principal characteristics of this study is that it could be useful to assess relationships between physical activity and the immune system in free-living conditions targeted at gaining information on possible long-term adaptations that could be produced by regular physical activity in this population. In contrast, prior studies have mainly focused on the acute effects of exercise on the immune system under laboratory conditions. Moreover, the study's design will provide data on the possible contributions of different factors (overweight, obesity, physical activity/sedentarism and physical fitness) to the immunological status of adolescents. These data may also serve to highlight the influence of these factors on metabolic disorders (dyslipidemias, glucose intolerance and metabolic syndrome). Further, we should be able to glean information on physical activity and eating habits during school recess, which as far as we aware is a topic that has barely been touched. To obtain this type of information, two specific questionnaires have been created to help describe the habits of the adolescent population of Madrid in these specific areas.

The study has several limitations. Self reporting is one of the inherent problems affecting the quality of the information obtained in any inquiry through interviews and questionnaires. Infections and allergic processes are subject to seasonal change such that gathering information at one specific point in time will not precisely reflect the prevalence and incidence rates of these disorders. Another possible limitation has to do with the response rates of the parents of the adolescents in the survey process. A reduced response rate could produce an undetermined bias in the responses, which could influence the conclusions drawn from the results.

The limitations of Study 3 are the restricted sample size (n = 200), which is the consequence of the high costs of the immunological study (approximately 600€/subject) and the labour intense data collection process involved in measuring physical activity using the accelerometer. This sample size does not allow for extrapolating results to the population group under study. However, it is sufficiently large to establish relationships among the variables determined. An additional limitation is the non-random selection of the components of the convenience sample, which could introduce a bias associated with the specific characteristics of the school populations of the centres selected.

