### Study aims

The main aim of the AFINOS Study (La Actividad Física como Agente Preventivo del Desarrollo de Sobrepeso, Obesidad, Alergias, Infecciones y Factores de Riesgo Cardiovascular en Adolescentes; Physical Activity as a Preventive Measure for Overweight, Obesity, Infection, Allergies and Cardiovascular Risk Factors in Adolescents) is to examine relationships between regular physical activity levels in adolescents and overweight, infection and allergies, along with metabolic and immune system markers used to evaluate their health status. Our working hypothesis is that adolescents who more often undertake physical activity (excluding intensive training targeted at sports performance) are healthier and enjoy a better quality of life. In addition, this study seeks to establish the general prevalence of overweight-obesity and immune system-related disorders (infections and allergies) in the study population (adolescents aged 13 to 16 living in the Madrid region). Also examined was the potential influence of the family environment and lifestyle in developing a disease or acquiring (un)healthy habits that could eventually lead to an obesity-related disorder.

The study includes three surveys conducted on three different study populations: (a) Study 1 performed on a sample of 2400 adolescents; (b) Study 2 on a sample comprised of the parents of these adolescents; and (c) Study 3 performed on 200 of the adolescents included in (a) to assess in detail their physical activity levels and health status. The aims of each of these sub-studies are outlined below:

(a) Aims of Study 1 conducted on a representative sample of adolescents living in the Madrid region

1. To determine the prevalences of overweight, obesity, infections and allergies.

2. To assess physical activity and sedentary habits.

3. To assess basic eating habits.

4. To assess the relationship between sedentary lifestyle and the prevalence of health disorders (obesity, infections and allergies).

5. To asses the relationship between sedentary lifestyle and academic performance.

(b) Aims of Study 2 conducted on the adolescents' parents

1. To assess physical activity and sedentary habits.

2. To assess basic eating habits.

3. To assess the relationship between sedentary lifestyle and the incidence of certain chronic diseases (obesity, infections, allergies, cardiovascular risk factors and metabolic or cardiovascular diseases).

(c) Combined aims of Studies 1 and 2

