## Methods/Design

The AFINOS Study is a multidisciplinary, cross-sectional, multicenter study endorsed by the National Research & Development & Innovation Plan of the Spanish Ministry of Education and Science, under the Strategic Line of Sport and Physical Activity. The three research groups involved are each specialized in a specific area of knowledge: (a) the Immunonutrition Research Group, Department of Metabolism and Nutrition, Scientific National Research Council (CSIC); (b) the Epidemiology Group, Department of Preventive Medicine and Public Health, Universidad Complutense de Madrid; and (c) the Physical Activity and Health Group. Department of Physical Education, Sport and Human Motricity, Universidad Autónoma de Madrid.

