### Research universe and study samples

The AFINOS Study takes as universe, the population of adolescents aged 13 to 16 of the Madrid region (central Spain) and their parents. The Madrid Region is one of the country's most densely populated areas. With an extension of 8028 km^2 ^representing a mere 1.5% of the geographic area of Spain, the Madrid province is home to 13.5% of the entire Spanish population. According to the 2006 census of the National Statistics Institute http://www.ine.es, in this year there were 228,535 adolescents aged 13 to 16 living in the Madrid region, representing 12.7% of the Spanish adolescent population of this age group. Of these adolescents, 104,725 lived in Madrid City, 100,610 in its suburbs and 23,200 in the villages of the region.

The sample size for Study 1 was calculated using the Schlesselmann formula [25] for known population sizes, taking 0.05 as the maximum permissible error (reliability of 95%). In the calculation, we used the estimated variance for obese plus overweight subjects in our population of 20% indicated by data from the AVENA national study [10].

The final sample size calculated at 1998 individuals was increased by 20% to compensate for possible dropouts or data losses to give a final sample size of 2400 adolescents of both sexes.

According to the geographic distributions of adolescents in the Madrid region: 46% of the sample (1058 subjects) was selected from Madrid City, 35% (805 subjects) from its suburbs and 19% (435 subjects) from its villages. A randomised cluster sample procedure was used to select the sample. The first level of sampling was the entire set of secondary schools of the Madrid region. Thus, of 25 schools selected, 10 schools were in the city, 8 in the suburbs, and 7 schools in villages. The second level of sampling was school classroom/grade (2nd, 3rd and 4th years of Compulsory Secondary Education and first year of Non-Compulsory Secondary Education, according to the Spanish education system). The sample for Study 2 was comprised of the parents of the adolescents selected for Study 1.

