#### Statistical analysis

The final data will be analyzed using SPSS and SAS software. Frequencies and distributions of the variables will be determined using descriptive statistics that will serve to determine the general situation of the study subjects. Quantitative variables will be expressed as means and standard deviations of the mean, except for age, which will be expressed as year-by-year frequencies (13-14-15 and 16), and qualitative variables will be expressed as absolute frequencies of every category and percentages related to the total number of valid cases. The normal distribution of quantitative variables will be checked through adequate tests. To determine possible associations, the Chi-squared test will be used for qualitative observations and the student *t-*test to compare independent means of the quantitative data [26]. Pearson's correlation coefficient will be used to analyse two quantitative variables and if these are not verified as normally distributed the Spearman correlation will be used [53]. When analysis of several variables is needed, a multivariate analysis using the forward stepwise multiple regression method will be performed to construct models to explain the variability observed in the population and assess the combined effect of different variables. Risk profiles will be generated by multiple logistic regression, determining adjusted regression coefficients to calculate the odds ratio for each variable.

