## Conclusions

In summary, the AFINOS Study seeks to gain insight into the lifestyle and health status of Spanish adolescents aged 13 to 16 years who live in the city of Madrid and its province. The study focuses on describing several health problems associated with the immunological status of the population (infections and allergies). In this way, it tries to evaluate the existing relationship between being overweight and habits of physical activity-sedentarism and the incidence of infections and allergies. Our exhaustive evaluation of the immunological and metabolic profiles of 200 adolescents will help us understand the existing link between physical activity habits or fitness levels and immunocompetence or metabolic health status. The results obtained in the convenience sample of this cross-sectional study will serve to undertake comparisons with the results of previous laboratory studies which seem to indicate that moderate exercise stimulates certain aspects of the immune response while intense exercise has undesirable effects [5]. In addition, the results obtained will serve to confirm previously reported findings of research into relationships between physical activity and being overweight or having a metabolic disorder in this age group [3].

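### The Discussion extends Study 2 from parents to all Madrid adults, and describes cross-sectional odds ratios in the language of risk and incidence; both inferences should be narrowed

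*Protocol article*

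**What the plan says.** **Design.** Methods/Design states: "The AFINOS Study is a multidisciplinary, cross-sectional, multicenter study". No follow-up is described. Under Data Collection, the adolescents fill in their questionnaire in one classroom session, and each parent receives one questionnaire to return a week later.

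**Who is sampled as an adult.** Research universe and study samples defines the universe as the region's 13- to 16-year-olds and their parents, and adds: "The sample for Study 2 was comprised of the parents of the adolescents selected for Study 1".

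**The adult statement.** The Discussion, in its paragraph on contributions and strengths, says that a high enough response may make it possible to estimate how common physical activity habits and sedentarism are, and the prevalence "of specific health habits in the adult population of the Madrid region". Response is the only condition given.

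**The risk statement.** The same paragraph says the data will "give an idea of the relative risks associated with sedentarism of developing the health problems for which information was collected".

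**Aims and conclusions.** Study 1 aim 4 is worded for the design: "To assess the relationship between sedentary lifestyle and the prevalence of health disorders (obesity, infections and allergies"). Study 2 aim 3 asks the parallel question in parents, but about the incidence of chronic diseases. The Conclusions relate overweight and activity habits to "the incidence of infections and allergies".

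**Planned measure.** Statistical analysis says: "Risk profiles will be generated by multiple logistic regression, determining adjusted regression coefficients to calculate the odds ratio for each variable".

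**Admitted limitations.** The limitations part of the Discussion says that data from one time point, with seasonal disorders, will not reflect prevalence and incidence precisely, and that low parental response could cause bias. It does not mention that parents are only part of the adult population.

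**The concern.** **Coverage.** Non-response and non-coverage are different errors. A high response rate limits the first. It does nothing about the second, because adults with no child among the selected pupils (young adults, childless adults, most older people) are never approached. A reader who accepts the article's condition would take a well-answered parent survey as a regional adult survey.

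**Risk language.** A relative risk of developing a disorder needs people free of it whose exposure is recorded before new cases arise. Here exposure and outcome are recorded together, so their order is unknown: overweight may have preceded inactivity as easily as followed it. The article's own Background separates cross-sectional from prospective evidence on activity and weight. In addition, the only effect measure named for binary outcomes is the odds ratio. For an outcome that is not rare it lies further from 1 than the ratio of prevalences, so reading it as a relative risk makes the association with sedentarism look stronger than it is.

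**Working it through.** The article gives no figure for either statement, so there is nothing to reproduce. Both gaps can be checked directly.

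**1. Adult coverage**

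Let w be the share of Madrid adults who are parents of 13- to 16-year-olds, and d the difference in prevalence of a habit between those parents and other adults. With complete and accurate response from parents:

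bias in the adult prevalence = (1 − w) × d

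The response rate does not appear in the formula, so raising it cannot reduce this bias. Neither w nor d is in the article. On assumed values, with d in percentage points:

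| w (assumed) | d = 5 | d = 10 | d = 20 |
|---|---|---|---|
| 10% | 4.5 | 9.0 | 18.0 |
| 20% | 4.0 | 8.0 | 16.0 |
| 30% | 3.5 | 7.0 | 14.0 |

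Across this range the bias at 100% response runs from 0.70 × 5 = 3.5 to 0.90 × 20 = 18 points. If d were zero there would be no bias, but Study 2 observes no other adults and so cannot show that.

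**2. Odds ratio against prevalence ratio**

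With p0 the prevalence in the unexposed:

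prevalence ratio = OR / (1 − p0 + p0 × OR)

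The one relevant figure in the article is 20% for overweight plus obesity, used in the Study 1 sample size. It is an overall figure; using it for the unexposed is an assumption. The odds ratios and the other values of p0 are assumptions too.

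- OR 2, p0 = 20%: 2 / (0.80 + 0.40) = 1.67
- OR 2, p0 = 5%: 2 / (0.95 + 0.10) = 1.90
- OR 2, p0 = 40%: 2 / (0.60 + 0.80) = 1.43
- OR 1.5, p0 = 20%: 1.5 / (0.80 + 0.30) = 1.36
- OR 3, p0 = 20%: 3 / (0.80 + 0.60) = 2.14

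The gap is small for an uncommon outcome and grows as the outcome becomes more common.

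**3. From prevalence ratio to risk of developing disease**

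No arithmetic closes this step. Even an exact prevalence ratio compares existing disorders between groups classified at the same time. Study 1 aim 4 is phrased accordingly; Study 2 aim 3, the Conclusions and the Discussion sentence are not.

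**The case against.** The strongest reply is that these are a few cautious phrases, not the plan. The Discussion only offers an idea of relative risks and says adult estimates may be possible. The adult sentence covers activity, sedentarism and certain health habits, not prevalence in general. The universe is already defined as adolescents and their parents, and no aim asks for adult prevalences. The analysis section nowhere says that odds ratios will be read as relative risks, and an odds ratio is a valid measure of association in a cross-sectional study. The infection questions are not reproduced; if they ask about episodes over a recall period, they count something other than point prevalence. The single time point is admitted as a limitation.

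Much of this stands. A reader might infer that the article promises both results, that both would necessarily be wrong, or that logistic regression must be replaced. The documents support none of these: the wording is hedged, the size of the adult error is unknown, and prevalence odds ratios are legitimate if so labelled. Nor does the article give any prevalence for infections, so it cannot be said how far an odds ratio would overstate the ratio for them.

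Three things remain. The hedge on the adult statement names the wrong condition, since response cannot supply coverage, and the limitations are silent on coverage. The incidence wording is not confined to the Discussion and Conclusions; it stands in a formal aim of Study 2. The admitted time-point limitation concerns seasonality and precision, not whether the risk of developing a disorder can be estimated. Even episodes counted over a recall period would precede or coincide with the recorded exposure.

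**Conclusion.** The point holds as one of interpretation. Study 2 can support statements about parents of adolescents aged 13 to 16 in the Madrid region, subject to response; it cannot support adult-population prevalences at any response rate without assuming that these parents resemble other adults. The resulting error is unknown: 3.5 to 18 percentage points on purely assumed inputs, and none if the groups do not differ.

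The cross-sectional data support associations with prevalence, not relative risks of developing disorders or relationships with incidence. Reading an assumed odds ratio of 2 as a relative risk would overstate a prevalence ratio of about 1.67 if the overall 20% applies to the unexposed, and of 1.90 to 1.43 as the assumed unexposed prevalence goes from 5% to 40%. The sample size and the planned logistic regression are unaffected.

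**What to change.** 1. **Discussion, adult statement:** delete it, and confine Study 2 inference to parents of adolescents aged 13 to 16 in the Madrid region, in line with the universe already defined.
2. **Discussion, limitations:** next to parental response, add that adults without a child in the sampled group are not covered, and that response cannot correct this.
3. **Discussion, risk statement:** describe cross-sectional associations between sedentarism and the prevalence of the recorded health problems.
4. **Study 2 aim 3 and Conclusions:** replace incidence with prevalence. If the infection questions use a recall period, say reported episodes in that period.
5. **Statistical analysis:** label the odds ratios as prevalence odds ratios and state that they are not to be read as relative risks. Adding prevalence ratios for common outcomes is optional.

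The cost is a few sentences. No new data or change of sample size is needed, and the planned model stays. The price is a narrower claim for Study 2 and more modest language about sedentarism.

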## Conclusions

In summary, the AFINOS Study seeks to gain insight into the lifestyle and health status of Spanish adolescents aged 13 to 16 years who live in the city of Madrid and its province. The study focuses on describing several health problems associated with the immunological status of the population (infections and allergies). In this way, it tries to evaluate the existing relationship between being overweight and habits of physical activity-sedentarism and the incidence of infections and allergies. Our exhaustive evaluation of the immunological and metabolic profiles of 200 adolescents will help us understand the existing link between physical activity habits or fitness levels and immunocompetence or metabolic health status. The results obtained in the convenience sample of this cross-sectional study will serve to undertake comparisons with the results of previous laboratory studies which seem to indicate that moderate exercise stimulates certain aspects of the immune response while intense exercise has undesirable effects [5]. In addition, the results obtained will serve to confirm previously reported findings of research into relationships between physical activity and being overweight or having a metabolic disorder in this age group [3].

